### Participants

This pilot will enroll licensed primary care clinicians, including physicians, nurse practitioners, and physician assistants. Inclusion criteria require health care providers to have ≥0.5 full-time equivalent dedicated to adult diabetes care at participating sites, the ability to complete 2 simulation periods, and provision of informed consent. Exclusion criteria include prior participation in any FibroX usability or validation studies, exclusive practice in pediatrics or nondiabetes specialty areas, or inability to complete all study procedures. Participating clinicians are expected to have varying levels of clinical experience, reflecting real-world primary care practice, but all are required to have active involvement in the management of adult patients with T2D to ensure familiarity with relevant clinical workflows and decision-making. Participants will be recruited through email invitations and departmental announcements across Yale-affiliated primary care and diabetes clinics, as well as participating federally qualified health centers. Recruitment will target clinicians with active involvement in the management of adults with T2D, with participation on a voluntary basis.

The simulation case library will comprise adult patients (aged ≥18 years) with T2D and at least one additional MASLD risk factor (eg, obesity, dyslipidemia, and hypertension). Each case must have a ground-truth fibrosis stage determined by liver biopsy or expert consensus based on VCTE. To ensure fidelity to real-world clinical presentation, cases will include complete routine clinical data such as age, AST, ALT, platelet count, HbA_1c_, BMI, and creatinine or estimated glomerular filtration rate, along with relevant clinical notes. The simulation case library will be developed using deidentified or synthetic cases derived from representative clinical datasets and prior cohorts, with case selection designed to capture a range of fibrosis risk profiles and clinical presentations. Cases will be curated to ensure clinical realism, balanced representation across fibrosis stages, and inclusion of all variables required for FibroX and comparator assessments.

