### Outcomes

The primary end points of this pilot study are the feasibility and usability of FibroX-enabled care within diabetes-focused clinical workflows. Feasibility will be assessed using recruitment and study completion rates, with prespecified targets of enrolling at least 70% of eligible clinicians and achieving a completion rate of at least 85% among enrolled participants. Completion will be defined as participants completing both simulation periods, including all assigned cases and postperiod surveys. Participants who do not complete both periods or required assessments will be classified as incomplete. Usability will be evaluated using the System Usability Scale (SUS), with a prespecified success threshold of 70 or higher.

Secondary end points include workflow efficiency and preliminary diagnostic performance. Workflow efficiency will be assessed by median time per case, with an anticipated threshold of 3.5 minutes or less. Preliminary diagnostic performance outcomes will include sensitivity, specificity, and the area under the receiver operating characteristic curve for the detection of MASLD-associated advanced fibrosis. Calibration will be examined using intercept, slope, and graphical assessment of predicted versus observed risk.

Exploratory end points will include clinician trust and cognitive workload, assessed using the AI trust scale and National Aeronautics and Space Administration Task Load Index (NASA-TLX), respectively, as well as implementation-related outcomes, including the proportion of guideline-concordant referrals and net reclassification improvement. Qualitative debrief interviews will further explore clinician understanding, interpretability, and perceived usefulness of the SHAP-based explanations, including how these outputs influence decision-making and trust in the model. These measures are intended to provide pilot estimates and inform the design, end point selection, and sample size considerations for a future definitive trial.

At a high level, this pilot will be considered successful if predefined feasibility and usability thresholds are met, including adequate recruitment and completion rates and a SUS score of 70 or higher, alongside signals of acceptable workflow efficiency and improved or comparable diagnostic performance relative to usual care. These criteria are intended to determine whether progression to a larger, real-world trial is justified.

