### Statistical Analysis

All analyses will follow an intention-to-treat principle, including all health care provider decisions regardless of sequence assignment. The primary comparison of diagnostic accuracy between FibroX-enabled care and usual care will use paired analyses to account for the crossover design. Sensitivity and specificity for detecting MASLD-associated advanced fibrosis will be compared using McNemar test for paired proportions. Overall discrimination will be assessed by calculating the area under the receiver operating characteristic curve for each condition, and calibration will be evaluated through intercept, slope, and calibration plots to determine agreement between predicted probabilities and observed outcomes.

To account for clustering at the health care provider level and the crossover design, mixed-effects logistic regression models will be used, specifying health care provider as a random effect and study condition, study period, and sequence assignment as fixed effects. Sensitivity analyses will also assess whether diagnostic performance differs by sequence assignment or period, which may suggest residual carryover or learning effects. These models will also adjust for case-level covariates such as age, BMI, and HbA_1c_ to explore potential confounding and heterogeneity. Secondary analyses will include net reclassification improvement to quantify whether FibroX improves assignment of cases into clinically appropriate triage categories compared with usual care. Bootstrap resampling will be used to generate CIs for net reclassification improvement and calibration metrics, ensuring robust estimation under small-sample conditions.

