Feasibility outcomes, including recruitment and completion rates, will be summarized descriptively with proportions and 95% CIs. Usability and trust scores from the SUS and AI trust scale will be analyzed using paired *t* tests or Wilcoxon signed-rank tests, depending on distributional assumptions. Cognitive workload scores from NASA-TLX will be compared similarly. Subgroup analyses will explore whether diagnostic performance varies across diabetes-related characteristics such as HbA_1c_, BMI, and duration of diabetes, using interaction terms in mixed-effects models. Missing data are expected to be minimal; if more than 5% of survey data are missing, multiple imputation under a missing-at-random assumption will be applied, with sensitivity analyses conducted using complete-case data. All statistical tests will be 2-sided with an α level of .05, and analyses will be performed using the R (R Foundation for Statistical Computing) or Python (Python Software Foundation) statistical packages.

To aid interpretation of the crossover design, sequence, period, and potential carryover effects will be explicitly examined. Sequence effects (AB vs BA) will assess whether the order of exposure to FibroX influences outcomes. Period effects will evaluate whether outcomes differ between the first and second study periods, independent of the intervention, which may reflect learning or temporal effects. Potential carryover effects will be explored by assessing interaction terms between intervention and study period and by comparing outcomes across sequences; a significant difference by sequence or interaction with period would suggest residual carryover. If meaningful carryover effects are detected, sensitivity analyses restricted to first-period data will be performed.

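### As listed, the mixed models carry one FibroX effect and no fibrosis-status term, so a fit to all decisions gives a stage-mix-weighted effect rather than sensitivity and specificity effects, and its subgroup interactions can be spurious

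*Protocol article*

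**What the plan says.** All references are to the protocol article.

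- **End points (Outcomes).** "Preliminary diagnostic performance outcomes will include sensitivity, specificity, and the area under the receiver operating characteristic curve" for advanced fibrosis. These are secondary, but the same section makes improved or comparable diagnostic performance part of the case for moving to a larger trial.
- **Named test (Statistical Analysis).** "Sensitivity and specificity for detecting MASLD-associated advanced fibrosis will be compared using McNemar test for paired proportions".
- **Clustered analysis (Statistical Analysis).** To handle clinician clustering and the crossover, the plan turns to mixed-effects logistic regression. The terms it lists are these: "specifying health care provider as a random effect and study condition, study period, and sequence assignment as fixed effects". Then: "These models will also adjust for case-level covariates such as age, BMI, and HbA_1c_ to explore potential confounding and heterogeneity". The section opens by including every clinician decision on an intention-to-treat basis. It does not name the models' dependent variable or restrict them to a class of cases.
- **Subgroups (Statistical Analysis).** "Subgroup analyses will explore whether diagnostic performance varies across diabetes-related characteristics such as" HbA1c, BMI and duration of diabetes, through interaction terms in the mixed models.
- **Known status (Participants).** "Each case must have a ground-truth fibrosis stage determined by liver biopsy or expert consensus based on VCTE". The library is to be balanced over fibrosis stages. No F3+ share is given, and nothing is said about stage balance within levels of BMI, HbA1c or diabetes duration.
- **Case sets (Trial Design and Oversight).** The two periods use different cases, so no clinician judges the same case twice.

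**The concern.** Sensitivity is defined only among F3+ cases and specificity only among <F3 cases. A model with one condition effect, fitted to both classes together, estimates neither. If the outcome is a correct call, the effect mixes the two changes in proportions set by case curation. If the outcome is a positive call, it shows only whether FibroX changes how often clinicians call advanced fibrosis.

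The McNemar test does not make up for this. It treats pairs as independent, so it ignores clustering by clinician, and the design supplies no pair in which one clinician judges one case under both conditions. The mixed model is therefore the analysis that could carry the sensitivity and specificity comparison, and as listed it is not tied to status.

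Two things are at stake. A loss of specificity could sit unseen inside a favourable pooled result that feeds the progression decision. And BMI, HbA1c or diabetes duration could appear to modify the FibroX effect only because they track fibrosis status.

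**Working it through.** **1. The plan's own figure.** Sample Size gives 36 or more clinicians, 32 cases each, 1150 to 1280 decisions, accuracy 0.60 vs 0.75, and power above 80%.

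- Count: 36 × 32 = 1152 and 40 × 32 = 1280. This reproduces.
- Power: with within-pair correlation 0 (assumed), the discordant share is 0.60 × 0.25 + 0.40 × 0.75 = 0.45. McNemar at two-sided 0.05 then needs 155 pairs for 80% power. The claim holds up to a design effect of 1152/155 = 7.4, or 576/155 = 3.7 if the 32 cases cover both periods (36 × 16 = 576). The protocol gives no design effect, so this checks only the inequality.

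This figure concerns overall accuracy. It says nothing about sensitivity or specificity separately.

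**2. What one pooled effect can hide.** Pooled accuracy = p × sensitivity + (1 − p) × specificity, where p is the F3+ share. The protocol gives no rates by stage, so those below are assumptions. At p = 0.5, three patterns give the same 0.60 vs 0.75:

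- (a) sensitivity and specificity both 0.60 to 0.75;
- (b) sensitivity 0.50 to 0.80, specificity 0.70 unchanged: (0.50 + 0.70)/2 = 0.60 and (0.80 + 0.70)/2 = 0.75;
- (c) sensitivity 0.45 to 0.85, specificity 0.75 down to 0.65: (0.45 + 0.75)/2 = 0.60 and (0.85 + 0.65)/2 = 0.75.

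In large simulated data sets (4000 clinicians, clinician SD 0.5 on the logit scale), the pooled odds ratio was 1.92, 1.92 and 1.90. Separate fits by status gave sensitivity/specificity odds ratios of 1.93/1.92, 3.72/0.99 and 6.13/0.62. The same listed terms, fitted by class, tell the three apart; the pooled fit does not.

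If the outcome were a positive call, pattern (a) would show nothing: 0.5 × 0.60 + 0.5 × 0.40 = 0.50 under usual care and 0.5 × 0.75 + 0.5 × 0.25 = 0.50 with FibroX.

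**3. Dependence on stage mix.** Assume sensitivity 0.60 to 0.85 and specificity 0.60 to 0.50. The pooled change is 0.25p − 0.10(1 − p) = 0.35p − 0.10: +7.5 points at p = 0.5, +4.0 at 0.4 (five equal stages, two of them F3+), −3.0 at 0.2 and −6.5 at 0.1. It turns negative only below p = 0.10/0.35 = 28.6%.

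**4. Subgroup interactions.** The simulation used 36 clinicians, 16 cases per period, a two-level subgroup, no true interaction within status, a logistic model with clinician-clustered standard errors standing in for the mixed model, and 600 runs per setting. Share of trials with a significant condition-by-subgroup term at 0.05, status left out:

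| Pattern | F3+ share 30% vs 70% | 40% vs 60% | 50% vs 50% |
|---|---|---|---|
| (a) | 5% | 6.5% | 5% |
| (b) | 53% | 18% | 5% |
| (c) | 92% | 43% | 5% |

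With status and condition-by-status added, the range over all nine cells was 4.5% to 6.3%. With 32 cases per period, (b) and (c) rose to 81% and 99.5% at 30% vs 70%; the status-adjusted rate reached at most 7%.

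A second simulation (400 trials, 36 clinicians × 32 decisions, logistic GEE) assumed F3+ in 5/8 of high-BMI and 2/8 of low-BMI cases, sensitivity 0.45 to 0.80 and specificity 0.70 to 0.72 in both groups. The apparent accuracy gain is 0.625 × 0.35 + 0.375 × 0.02 = 22.6 points vs 0.25 × 0.35 + 0.75 × 0.02 = 10.3 points. The interaction was significant in 56% of trials without status terms and 7% with them (odds ratio 1.71 vs 0.99).

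**The case against.** The strongest reply is that the text leaves these points open rather than settling them wrongly. It speaks of models in the plural, names no outcome or case subset, and gives covariates as examples. Fitted separately to F3+ and <F3 cases, the listed terms are sufficient, and that detail may sit in an analysis plan that is not shown. This stands in part. A reader might infer that the models cannot estimate sensitivity or specificity effects at all; the document does not support that. Still, the article chose to list the model's terms and to include all decisions, and nothing in it ties the FibroX effect to status.

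It is also fair that overall accuracy is a legitimate quantity: the study is sized on it, and a pooled model estimates it. It is not, however, the sensitivity and specificity named under Outcomes.

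Three further inferences go too far:

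- **That the pooled effect may change sign here.** Under the rates assumed above this needs fewer than about 29% F3+ cases, which a stage-balanced library makes unlikely.
- **That the subgroup results are confounded as a matter of course.** The bias needs both unequal FibroX effects by status (on the logit scale) and an F3+ share that differs across the subgroup. With either absent, rejection in the table stays at about 5% to 6.5%. The subgroup analyses are also described as exploratory.
- **That omitting stage within class (F3 vs F4, F0 to F2) is an error.** Sensitivity and specificity for F3+ are defined across those stages; adding stage could only serve precision.

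**Conclusion.** The point holds in conditional form. If the listed models are fitted to all decisions together, their single FibroX effect is a pooled one that cannot separate sensitivity from specificity; a rise of 15 points in both and a rise of 40 with a fall of 10 look the same at 50% F3+. This matters because the one test named for those end points is unsuited to clustered decisions without same-clinician, same-case pairs. The subgroup interactions can be spurious, with false-positive rates from near nominal to 92% at 16 cases per period, depending on how far the FibroX effect and the F3+ share differ. Every stage-specific rate and subgroup imbalance behind these figures is an assumption. The change should be made before analysis, though the end points affected are secondary and exploratory.

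**What to change.** State the outcome as a correct call, with clinician as a random effect and condition, period and sequence as fixed effects, in one of two ways:

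- separate models for F3+ and <F3 cases; or
- one model with status and condition-by-status added.

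Report a sensitivity difference and a specificity difference, each with a confidence interval that respects clustering. Keep status and condition-by-status in every subgroup model, or test the interaction within each class, before reading anything into HbA1c, BMI or diabetes duration. Stage within class may be added as an optional precision covariate. A pooled accuracy effect may be kept as a labelled summary, with the library's F3+ share stated beside it.

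The cost is a few sentences: stage is recorded for every case, and recruitment had not begun at submission. The downside is two somewhat wider intervals in place of one pooled effect.

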### Interventions

The intervention arm, known as FibroX-enabled care, will use a simulated EHR-like interface delivered through a secure web-based platform that mirrors the presentation of routine outpatient clinical information. Participants will review standardized simulated cases containing patient demographics, relevant clinical history, laboratory data, and clinical notes. Within this interface, FibroX-enabled care will display key predictive and explanatory information at the point of decision-making. This will include individualized FibroX risk estimates for advanced fibrosis generated using routinely available clinical data. Crucially, the interface presents dual-threshold triage bands aligned with established clinical guidance, classifying patients into 3 actionable categories: rule out, indeterminate (with a pathway to VCTE or other noninvasive testing), and rule in (with a pathway to hepatology referral). In addition, the interface presents case-level SHAP outputs that display the relative contribution of individual clinical variables (eg, age, AST, ALT, platelet count, HbA_1c_, BMI, and kidney function) to the predicted risk of advanced fibrosis. These explanations are presented in a structured visual format, such as ranked feature contributions, alongside the risk estimate and triage category to support clinician interpretation at the point of decision-making. By providing case-level explanations of the key drivers of predicted risk, these SHAP-based outputs are intended to support clinician interpretation of the model’s recommendations, increase confidence in triage decisions, and facilitate more consistent application of guideline-concordant referral pathways compared with usual care, where risk estimation is often implicit and variable.

The comparator arm, designated as usual care, will present the same standardized clinical case information within the simulated EHR-like interface but without FibroX risk estimates, SHAP explanations, or AI-based triage support. Participants in this arm will make diagnostic and management decisions based on routine clinical judgment alone. Optional access to a basic FIB-4 calculator will be provided, reflecting common clinical practice for noninvasive fibrosis risk stratification. FIB-4 is a widely used blood-based fibrosis score derived from age, AST, ALT, and platelet count to estimate the likelihood of advanced fibrosis [23].

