### Participant Timeline and Study Schedule

This health care provider–level crossover pilot is planned over a 12-month period. Months 0 to 2 will be used for finalizing the platform and completing quality assurance of the simulated case library. The first study period will then be conducted during months 2 to 4, followed by a 1-week washout period to reduce potential carryover effects. The second study period will take place during months 4 to 6. After completion of both periods, participants will complete postperiod surveys assessing usability, trust, and cognitive workload, followed by brief semistructured debrief interviews. The remaining months will be dedicated to data cleaning, analysis, qualitative review, and final reporting.

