### Data Collection Methods

The platform automatically logs case navigation, decisions, timestamps, and use of FibroX features and overrides. Clinicians will not receive case-level performance feedback during either simulation period. Feedback, if provided, will be deferred until completion of the study period to minimize within-period learning effects. Surveys (SUS, AI trust, and NASA‑TLX) are administered electronically at the end of each period. Qualitative debriefs are audio-recorded and transcribed for thematic analysis. Completeness checks and range validations occur at ingestion.

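### Usability of FibroX-enabled care is judged against an absolute SUS of 70, but the only stated SUS analysis is a paired test of the difference from usual care; AI trust is paired with a condition that has no AI

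*Protocol article*

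**What the plan says.** The Outcomes section names the primary end points as "the feasibility and usability of FibroX-enabled care within diabetes-focused clinical workflows". For usability it states: "Usability will be evaluated using the System Usability Scale (SUS), with a prespecified success threshold of 70 or higher". The last paragraph of that section uses the same threshold as a progression criterion, listing "adequate recruitment and completion rates and a SUS score of 70 or higher" among the conditions for calling the pilot a success.

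The Statistical Analysis section treats the two primary end points differently. For feasibility: "Feasibility outcomes, including recruitment and completion rates, will be summarized descriptively with proportions and 95% CIs". For usability, the next sentence reads "Usability and trust scores from the SUS and AI trust scale will be analyzed using paired" t tests or Wilcoxon signed-rank tests, depending on distribution. That sentence covers the AI trust scale as well, and NASA-TLX is to be handled in a similar way.

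The Interventions section describes usual care as the same case interface "without FibroX risk estimates, SHAP explanations" or AI-based triage, with an optional FIB-4 calculator.

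On timing, Data Collection Methods says that the three surveys "are administered electronically at the end of each period", and Table 1 ticks SUS, AI trust and NASA-TLX in both intervention periods. Participant Timeline and Study Schedule says: "After completion of both periods, participants will complete postperiod surveys assessing usability, trust, and cognitive workload".

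**The concern.** The criterion concerns a level: does FibroX-enabled care reach 70? The stated analysis concerns a difference between conditions. A significant paired result does not show that 70 was reached, and a null result does not show that it was missed. If the analysis section is followed as written, the report on a primary end point would centre on a P value unrelated to its success rule. The uncertainty around the figure that decides progression would not be among the stated results.

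The AI trust scale raises a related problem. A paired difference needs a score with a comparable meaning in both conditions, and usual care gives the clinician no AI output to rate. Both paired analyses also depend on a survey after each period, and the article's sections do not agree on that.

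**Working it through.** The article gives no SD, power or precision figure for SUS or AI trust, so there is no stated figure to reproduce. The sample size statement concerns diagnostic accuracy and does not bear on this point.

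**1. What the paired test estimates.** SUS is collected in both periods (Data Collection Methods, Table 1), and each clinician has one FibroX period and one usual care period. The pair is therefore FibroX and usual care. The article does not write this out, but the two-condition design implies it.

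**2. Inputs.**
- From the article: n = 36 (minimum enrolment); completion target 85%, and 0.85 × 36 = 30.6, about 31; threshold 70; two-sided α = 0.05.
- Assumed, because the article gives neither: SUS SD 10 to 20; within-clinician correlation ρ 0.3 to 0.5.

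**3. Can the paired test and the criterion disagree?** Paired power comes from the noncentral t distribution with SD_diff = SD × √(2(1 − ρ)) and noncentrality (difference / SD_diff) × √n. The chance that the observed FibroX mean reaches 70 is 1 − Φ((70 − μ) / (SD/√n)). With n = 36:

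- *True SUS 65 with FibroX, 55 with usual care.* SD 20, ρ 0.3: SD_diff = 23.7, noncentrality = (10/23.7) × 6 = 2.5, power 0.69. SD 10, ρ 0.5: SD_diff = 10, noncentrality 6, power above 0.99. The chance of a FibroX mean of 70 or more is 1 − Φ(5/3.33) = 0.07 for SD 20 and 1 − Φ(5/1.67) = 0.001 for SD 10. The paired test is usually significant while the criterion is nearly always missed.
- *True SUS 76 in both conditions.* The paired test rejects only at its 5% error rate. The chance of a FibroX mean of 70 or more is 1 − Φ(−6/3.33) = 0.96 for SD 20 and above 0.99 for SD 10. The criterion is nearly always met while the paired test shows nothing.

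**4. What a direct estimate would show.** The 95% CI half-width of the FibroX mean is t(0.975, n − 1) × SD/√n:

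| n | SD 10 | SD 15 | SD 20 |
|---|---|---|---|
| 36 | 3.4 | 5.1 | 6.8 |
| 31 | 3.7 | 5.5 | 7.3 |

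For example, an observed mean of 71 with SD 15 and n = 36 has a 95% CI of 71 ± 5.1, or 65.9 to 76.1. The choice of rule also matters. If the lower limit had to reach 70, the observed mean would need to be at least 73.4 to 76.8 (n = 36) or 73.7 to 77.3 (n = 31).

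**5. AI trust by sequence.** No arithmetic applies. In sequence BA the usual care score is taken in period 1, before any exposure to FibroX in the trial. In sequence AB it is taken in period 2, after FibroX. The usual care score therefore has a different meaning in each sequence, and the paired difference mixes the two.

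**6. Survey timing.** Data Collection Methods and Table 1 give two administrations, one per period. The timeline section places the surveys after both periods, while still calling them postperiod surveys. Which applies decides whether the pairs are collected as planned. It also touches the completion end point, whose definition requires the postperiod surveys.

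**The case against.** The strongest reply is that the Outcomes section already contains the decision rule. Checking it needs only the FibroX-period scores, which are to be collected, and nothing says that the paired test decides success. The Sample Size section also expects adequate precision for usability metrics, so some interval is evidently intended. A condensed article may leave the choice of mean, median or confidence limit to a fuller plan. The paired SUS comparison is legitimate in itself, because the usual care interface can be rated.

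Much of this stands. A reader might infer that the primary usability end point cannot be judged, or that the progression decision would come out wrong; the documents do not support that. The bare absence of a summary rule is not the point either. What remains is that the article does state an analysis for SUS, and that analysis answers a different question, while the neighbouring sentence gives the feasibility outcomes an estimate with a CI.

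On AI trust, the scale's items are not shown. If they ask about clinical AI in general, a rating before exposure is answerable, so it would go too far to say that usual care scores cannot be given. Trust is also exploratory and enters no success criterion. The planned examination of sequence and carryover effects would not turn the paired trust difference into a clean condition effect.

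On timing, it is tempting to conclude that no paired scores would exist. That does not follow, since clinicians surveyed at the end could still rate each condition. The sections conflict, and no more than that can be said.

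**Conclusion.** The point holds as a mismatch between a primary criterion and its stated analysis. The paired test estimates a difference from usual care and gives no estimate or uncertainty for the FibroX level that is judged against 70. The threshold remains checkable descriptively, so this should be corrected but does not invalidate the trial. The uncertainty left unstated is about 3.4 to 7.3 SUS points on either side of the mean for 31 to 36 clinicians. That range rests wholly on an assumed SD of 10 to 20 and illustrates ordinary pilot imprecision, not harm caused by the paired test. The disagreement probabilities rest on the same SDs and on an assumed correlation of 0.3 to 0.5.

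The AI trust and survey-timing parts are lesser: the first concerns the interpretation of an exploratory measure, the second an internal conflict to be reconciled.

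**What to change.** - In Statistical Analysis, state the primary usability analysis as the mean SUS from the FibroX period (period 1 in AB, period 2 in BA), with a 95% CI, judged against 70 among all clinicians exposed to FibroX. State whether the mean or its lower limit must reach 70.
- Keep the paired SUS and NASA-TLX comparisons, labelled as secondary to that analysis.
- Summarize AI trust from the FibroX period only, with a CI, and drop its paired test. The survey can then be left out of the usual care period.
- Change the timeline section so that surveys fall at the end of each period, as Data Collection Methods and Table 1 have it.

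The cost is a few sentences and one survey fewer per clinician. The only loss is a usual care trust score that is hard to interpret. The article reports that recruitment had not begun at submission, so on that timeline the change can be made before any data are seen.

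### The between-condition tests of SUS, AI trust and NASA-TLX carry no period term, although the diagnostic model adjusts for period and sequence

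*Protocol article*

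**What the plan says.** Protocol article, Statistical Analysis. The sentence on the first two scores begins "Usability and trust scores from the SUS and AI trust scale will be analyzed using paired". It names the t test and, as the alternative for the same differences, "Wilcoxon signed-rank tests, depending on distributional assumptions". The next sentence extends this to workload: "Cognitive workload scores from NASA-TLX will be compared similarly". No period or sequence term is named for any of the three scores.

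For diagnostic decisions the same section plans mixed-effects logistic models "specifying health care provider as a random effect and study condition, study period, and sequence assignment as fixed effects". It says that differences by sequence or period in diagnostic performance are something "which may suggest residual carryover or learning effects", and that period differences in outcomes generally are something "which may reflect learning or temporal effects". Its last paragraph adds that "sequence, period, and potential carryover effects will be explicitly examined". The only action attached to that examination is a sensitivity analysis restricted to the first period if meaningful carryover is found.

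Data Collection Methods and Table 1 place the three surveys in each period, so each score belongs to one period and one condition. Randomization is 1:1 to the two sequences.

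**The concern.** In sequence AB, FibroX is used in period 1. In BA it is used in period 2. The within-clinician difference (FibroX minus usual care) therefore contains the period effect with a minus sign in AB and a plus sign in BA. A one-sample test on the pooled differences treats that systematic gap between sequences as random scatter. Familiarity with the platform could plausibly shift workload or usability ratings in period 2 whatever the condition, and the plan itself names learning as a possibility.

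At stake is the reported precision of these comparisons. The Outcomes section wants the pilot estimates to inform end point selection and sample size for a later trial. An SD of differences that contains a period effect is a poor input for that purpose.

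**Working it through.** **Inputs from the protocol.** At least 36 clinicians (Sample Size); 1:1 allocation, so 18/18 if balanced (Randomization); two-sided α of .05 (Statistical Analysis); completion target of at least 85%, where 0.85 × 36 = 30.6, about 31 completers (Outcomes).

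**Assumptions.** The protocol states no survey SD, no period effect and no power for any survey outcome, so there is no stated figure to reproduce. The unit is the within-sequence SD of the within-clinician difference, set to 1. The condition effect is τ = 0.4. The period shift π (period 2 minus period 1) is varied from 0 to 1. Differences are normal with mean τ − π in AB and τ + π in BA.

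**Step 1: the estimate.** The pooled mean difference has expectation τ + π(nBA − nAB)/n. The adjusted estimate, the average of the two within-sequence means, has expectation τ. At 18/18 the two point estimates are identical, so only the standard error differs.

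**Step 2: the standard error.** The expected variance of the pooled differences is 1 + (nAB × nBA/n) × (2π)²/(n − 1). At 18/18 this is 1 + 9 × 4π²/35 = 1 + 1.0286π².
- π = 0.25: √1.0643 = 1.032
- π = 0.5: √1.2571 = 1.121
- π = 1: √2.0286 = 1.424

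The average ratio of standard errors in simulation was 1.03, 1.12 and 1.43.

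**Step 3: power and type I error at 18/18** (simulation of the paired t test against the period-adjusted crossover t test with n − 2 degrees of freedom; ranges reflect simulation error):

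| π | Paired t, power | Adjusted, power | Paired t, type I error |
|---|---|---|---|
| 0 | 64 to 65% | 64 to 65% | 0.050 |
| 0.25 | 62 to 63% | 64 to 65% | 0.044 |
| 0.5 | 55 to 56% | 64 to 65% | 0.029 |
| 1 | 32 to 33% | 64 to 65% | 0.006 |

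The exact power of the adjusted test, from the noncentral t distribution with 34 degrees of freedom, is 64.5%. The signed-rank test behaves in the same way. With τ = 0.5 its power is 0.746 at π = 0.5 and 0.508 at π = 1, against 0.833 for the adjusted t test.

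**Step 4: unequal sequences, 31 analysed, π = 0.5.** Bias = π(nBA − nAB)/n.
- 16 AB/15 BA: 0.5 × (−1)/31 = −0.016 SD
- 18 AB/13 BA: 0.5 × (−5)/31 = −0.081 SD
- 13 AB/18 BA: +0.081 SD

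If five losses from 36 fall at random, all five fall in BA with probability C(18,5)/C(36,5) = 2.3%. A 3/2 split has probability 66%.

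**Step 5: cost of adjusting when π = 0.** No visible loss at 18/18. At 18/13, power is about 58% unadjusted and 56 to 57% adjusted, so about one point is lost.

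**The case against.** The case on the other side is substantial, and much of it stands.

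- **Validity.** With 1:1 sequences the paired tests are unbiased and err on the conservative side. A reader might infer a risk of false positives; the calculation shows the opposite. This stands.
- **Bias through dropout.** A reader might infer that tolerating 15% dropout makes the estimate materially biased. That needs a lopsided split, can go in either direction, and overlooks the plan's own rule of multiple imputation when more than 5% of survey data are missing. Five clinicians missing one of two survey rounds is 5/72 = 6.9%, which would trigger the rule. Imputation may reduce the bias, though reliably only if its model contains sequence and period.
- **Learning.** A reader might infer that the plan expects learning effects. It says only that they may occur, and case-level feedback is withheld to limit within-period learning. At a shift of 0.25 SD the loss is about 2 points.
- **Weight.** The primary usability criterion is a SUS of 70 or higher, which does not use these tests. Trust and workload are exploratory, and no survey power is claimed.
- **Choice of test.** The rule for choosing between t and Wilcoxon is ordinary analysis-plan detail, and its absence here is no fault.
- **Period is already examined.** The plan says "Period effects will evaluate whether outcomes differ between the first and second study periods". This tempers the point but does not answer it: examining period separately leaves the survey comparison unadjusted, and a period effect without carryover triggers no action.

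**Conclusion.** The point holds as one of efficiency and internal consistency. The plan names a method for three scores measured in both periods that ignores a design factor it adjusts for elsewhere. With balanced sequences the cost is an overstated standard error: about 3%, 12% and 43% for period shifts of 0.25, 0.5 and 1 SD. Power falls by about 2, 9 and 32 points from about 65%. The shifts and the 0.4 SD condition effect are assumptions, and with no period effect nothing is lost.

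Bias is a secondary matter. For a 0.5 SD shift it is about 0.016 SD at 16/15 and reaches 0.08 SD, in either direction, only at an extreme 18/13 split, before any imputation. The documents do not support a claim that the primary usability decision is compromised or that these tests give spurious positive results. The change is still worth making before recruitment because it is nearly free and uses a structure the plan already has.

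**What to change.** Replace the paired-test sentences with wording such as: *Between-condition comparisons of SUS, AI trust and NASA-TLX scores will use a linear mixed model with condition, period and sequence as fixed effects and clinician as random effect. A rank-based analysis stratified by sequence will be the sensitivity analysis. Any imputation model will include sequence and period.* With complete data, the model's condition effect equals the average of the two within-sequence mean differences. The SUS threshold of 70 stays as it is.

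Also reconcile the survey timing. Participant Timeline and Study Schedule can be read as placing the surveys only after both periods, whereas Data Collection Methods and Table 1 place them in each period. Any paired or period-adjusted comparison needs the latter.

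The cost is a few lines of text, one degree of freedom, and at most about one power point if there is no period effect.
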